**Fig. 1 Fig1:**
[figure not shown]
Preliminary CONSORT diagram

### Recruitment

GPs will be recruited by emailing lists from professional organizations, phone calls to private practices, and word of mouth (Appendix 2 shows all documents given to GPs). GPs will then recruit their patients seen for routine visits at their practice (Appendix 3 shows all documents that GPs discuss with their patients).

### Study procedures

During the recruitment period, the study team will proactively contact GPs to ensure that patient enrolment is going as planned. The GPs will also complete questionnaires at the end of patient recruitment (T1, approximately 6 months after training) and at the end of patient follow-up (T2, approximately 12 months after training). Figure 2 shows the diagram of what is expected by GPs. Moreover, all GPs will also be asked in the T1 questionnaire to participate in a 30-min optional semi-structured interview (see interview guide in Additional file 1; Appendix Table 1). We will perform 10 to 15 interviews, and analyze transcripts using a process evaluation methodology to understand how GPs approach smoking cessation with their patients and how that changed when using default choices and an electronic decision aid.

**Fig. 2 Fig2:**
[figure not shown]
Diagram of expected role of general practitioners

### Blinding

The smoking cessation experts administering the trainings will not be blinded. GPs will be blinded. Their consent form will only tell them that the study is comparing two versions of a training about smoking cessation, and not the nature of differences between the intervention and enhanced usual care. Nonetheless, GPs in the control group may realize their training is shorter, and GPs in the intervention group will realize their training is significantly different from traditional teachings about smoking cessation. Patients will likewise only be told that the study compares two training programs, and not the precise nature of intervention. Those in the control group should not be conscious that they are receiving usual care, and not quit aids as the default choice or a decision aid. Outcome assessors will not be blinded to study arm when performing follow-up with GPs and patients, however care will be taken not to re-inforce teachings related to the intervention (i.e. use of the decision aid or default choices). The statistician performing the primary outcome analyses will be blinded to group assignments.

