### Controlling for contamination and other potential biases

Because this is a pragmatic study, there is a risk of co-administration of interventions and contamination between groups. We will be careful not to reinforce messages about default choices and SDM when contacting GPs about participant inclusion. While cluster-randomized controlled trials limit contamination between groups and better mirror routine clinical practice, they present special challenges not seen in traditional randomized controlled trials [20]. Because the unit of randomization is individual GPs but the unit of analysis is individual patients, there can be imbalances in patient-level confounders. Some clustering is addressed by using the intra-cluster correlation coefficient at the time of analysis. However, bias can come from the post-randomisation recruitment of patients. This bias is addressed by streamlining patient questionnaires, limiting post-randomisation selection bias, and reporting outcomes at both the cluster and individual level [21]. Under-recruitment by certain GPs can exacerbate imbalances, so a study coordinator blinded to treatment assignment will contact participating GPs within two weeks of the training and regularly thereafter to ensure that the inclusion process is functioning at their site.

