### Primary outcome measure

The primary outcome measure is smoking cessation. We will measure smoking cessation using the self-reported, 7-day point-prevalence smoking abstinence at six months follow-up after the baseline visit with a GP. Point-prevalence abstinence will be defined as self-reported absence of smoking or use of other tobacco-containing products (smokeless tobacco like iQos, snus, etc.) during the prior 7 days at the time of a follow-up phone call by the research team [21]. The point-prevalence of smoking abstinence at 6 months is a widely used measure in the smoking cessation literature that correlates closely with long-term abstinence. Use of an e-cigarette will not count as tobacco use.

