### Protocol amendments

The original ethics approval was received 15.02.2021 for Version 1.2 of all study documents. Since then, we have made amendments to clarify blinding procedures (study staff are not blinded when contacting GPs and patients during follow-up), to clarify the monitoring plan, to allow patients to complete the consent and T0 questionnaire at home and return directly to the central study site, to specify how GPs can withdraw from the study. Approval for V1.4 was obtained 15.02.2022.

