This study presents several weaknesses, including an incomplete blinding and that the recruitment of patients is realized after the randomization of the GPs. We also use of self-reported smoking cessation at 6 months and not biochemical data to reduce the complexity of the study for the patients. Moreover, we are only intervening with GPs at one time point, and GPs may only see their patients once, such that the intervention may not be sufficiently strong to observe an effect. Another limitation is that the intervention includes two elements (the course and the electronic decision aid) and it will not be possible to know which of the two elements will have induced the most change.

However, we believe that this study has the potential to change significantly our approach to smoking cessation in primary care, and could have worldwide implications. The underuse of smoking cessation aids in primary care has been reported anecdotally and in the scientific literature in multiple countries. Default choices and the electronic decision aid are low-cost, easily diffusible interventions.

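### The unverified, self-reported primary outcome is taken mainly by telephone by staff who know the arm, and no stated safeguard covers how they elicit or record the answer

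*Protocol article*

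**What the plan says.** The Primary outcome measure section defines the endpoint: "We will measure smoking cessation using the self-reported, 7-day point-prevalence smoking abstinence at six months follow-up after the baseline visit with a GP". The answer is given in a telephone call from the research team. The Outcomes section adds that mailed questionnaires serve patients who cannot be reached by telephone. The Discussion confirms that there is no objective check: "We also use of self-reported smoking cessation at 6 months and not biochemical data". Data management states that no biological samples are taken.

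On who knows the arm, the Blinding section says: "Outcome assessors will not be blinded to study arm when performing follow-up with GPs and patients". The Protocol amendments section describes the same position: "study staff are not blinded when contacting GPs and patients during follow-up". The precaution attached to this is: "however care will be taken not to re-inforce teachings related to the intervention". The section also says: "The statistician performing the primary outcome analyses will be blinded to group assignments". Patients are told only that two training programmes are being compared.

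The section on contamination and other biases describes a further role: "a study coordinator blinded to treatment assignment will contact participating GPs within two weeks of the training and regularly thereafter". That person's task is to see that patient inclusion is working at each site.

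**The concern.** The endpoint depends on one answer, with nothing to check it against, and the person who elicits and records it knows the arm. Even a narrow 7-day question leaves room for unequal follow-up questions, unequal acceptance of an ambiguous reply, or unequal handling of a lapse or a tobacco product other than cigarettes.

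The stated protections act elsewhere. Avoiding reinforcement limits contamination. Keeping patients unaware of the comparison limits bias in what they choose to report. A blinded statistician protects analytic decisions, but works on data already captured. The Discussion lists incomplete blinding and self-report as weaknesses but attaches no safeguard to either.

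The trial is sensitive to this because expected event rates are low. A few answers per hundred smokers, shifted in one arm, are a material share of the planned difference, and neither the P value nor any analysis of the collected data could separate that shift from a real effect.

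**Working it through.** **Inputs from the protocol (Sample size and power calculation):** abstinence 4% control and 10.5% intervention, so a difference of 6.5 points; two-sided alpha 0.05; 80% power; intraclass correlation 0.03; 20 GPs per arm with 20 patients each; recruitment target 46 GPs with 23 patients each, i.e. 23 × 23 = 529 per arm.

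**Assumed input:** f, the net excess fraction of continuing smokers in the intervention arm recorded as abstinent. The protocol gives no figure, so a range is shown.

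**Step 1. Reproduce the plan's own figure.** For two proportions without continuity correction:

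n = [1.96 × √(2 × 0.0725 × 0.9275) + 0.842 × √(0.04 × 0.96 + 0.105 × 0.895)]² / 0.065² ≈ 249 per arm.

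Design effect = 1 + 19 × 0.03 = 1.57. Then 249 × 1.57 = 391 per arm, and 391 / 20 = 19.5, rounded up to 20 clusters. The plan's figure is reproduced. Power at 20 × 20 per arm is 81%.

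**Step 2. Points added to the difference:** added difference = f × (1 − true abstinence in the intervention arm).

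| f | No true effect (96% still smoking) | Planned effect (89.5% still smoking) |
|---|---|---|
| 2% | 0.96 × 0.02 = 1.9 points (30% of 6.5) | 0.895 × 0.02 = 1.8 points (28%) |
| 4% | 0.96 × 0.04 = 3.8 points (59%) | 0.895 × 0.04 = 3.6 points (55%) |

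**Step 3. Fraction needed to reproduce the whole planned effect with no true effect:** 0.065 / 0.96 = 6.8%.

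**Step 4. False-positive rate with 4% true abstinence in both arms.** The recorded intervention rate is 4% + 0.96f. The chance of a significant result is the power of the same test at that rate, on the effective sample size: 400 / 1.57 = 255 per arm, or 529 / 1.66 = 319 per arm, where 1.66 = 1 + 22 × 0.03.

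| f | Recorded intervention rate | 400 per arm | 529 per arm |
|---|---|---|---|
| 0 | 4.0% | 5% | 5% |
| 2% | 5.9% | 17% | 20% |
| 3% | 6.9% | 30% | 36% |
| 4% | 7.8% | 45% | 54% |
| 6.8% | 10.5% | 81% | 89% |

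An observed difference of about 4.1 points (400 per arm) or 3.6 points (529 per arm) is enough for significance, so a bias well short of the full effect already matters.

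**Step 5. A second, smaller route.** Patients lost to follow-up count as smokers, so unequal effort to reach patients also moves the endpoint. If true abstinence were 10.5% in both arms and contact 95% against 85% (both assumed), the shift is 0.105 × 0.10, about 1 point.

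**The case against.** The unblinded follow-up is deliberate and disclosed, and a reason is given for omitting biochemical tests: to keep the study simple for patients. The patients, who supply the answer, are masked to the nature of the comparison. The question is narrow, with e-cigarettes explicitly not counted as tobacco use. Mailed replies and patients lost to follow-up are not open to a caller's miscoding. All of this stands. It makes a large f less plausible, and f has to be read as a net figure over all continuing smokers in the arm. It does not remove bias on the caller's side.

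Three stronger readings are tempting, and the document supports none of them.

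- A reader might infer that the protocol contradicts itself by promising a blinded coordinator. That coordinator monitors inclusion, and nothing says that this person collects the outcome. The passages are in tension over who contacts GPs, because the amendment describes unblinded staff contacting GPs during follow-up, but they can both be true.
- A reader might infer that a small recording bias could by itself produce the planned effect. At 2% it supplies less than a third of it.
- A reader might infer that the caller has no need to know the arm. The questionnaire content is in an appendix that is not shown, so this cannot be checked. Fixed wording and a suitable question order may already exist there.

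**Conclusion.** The point holds as an avoidable exposure of the primary outcome to observer bias. That assessors are unblinded, that the outcome is a self-report taken mainly by telephone, and that it is not verified are all explicit in the protocol. That the bias occurs, and how large it is, is not known.

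The calculations rest on misrecording in one arm and one direction, on the plan's 4% control rate and intraclass correlation of 0.03, and, for the false-positive rates, on no true effect. Under those assumptions, net misrecording of 2% to 4% would inflate the estimate materially and raise the false-positive rate several-fold. It would not replace the effect. The sample size calculation is unaffected. This is a worthwhile, low-cost improvement and does not invalidate the design.

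**What to change.** Amend the Blinding section so that the 6-month abstinence item is collected as follows:

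- The REDCap follow-up form and the call list show neither arm nor GP identity.
- Calls go, where possible, to existing staff who do not know the allocation.
- The 7-day tobacco question is asked first, in fixed wording, and the field is locked before any item on the decision aid or the GP's approach.
- The caller records whether the arm was known at the time of the answer.

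As a minor clarification, state consistently in the Blinding, contamination and amendments sections which staff contacting GPs are blinded (inclusion monitoring) and which are not (follow-up).

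The cost is a user-rights setting, a question order and a short amendment. No extra staff, patient burden or biochemical test is needed, and the endpoint and sample size stay as they are. The downside is imperfect masking: some existing staff may already know the allocation, and a patient may reveal the approach used. Hiding a field does not blind someone who already knows the arm, which is why the assignment of callers and the record of whether the arm was known both matter.

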### Controlling for contamination and other potential biases

Because this is a pragmatic study, there is a risk of co-administration of interventions and contamination between groups. We will be careful not to reinforce messages about default choices and SDM when contacting GPs about participant inclusion. While cluster-randomized controlled trials limit contamination between groups and better mirror routine clinical practice, they present special challenges not seen in traditional randomized controlled trials [20]. Because the unit of randomization is individual GPs but the unit of analysis is individual patients, there can be imbalances in patient-level confounders. Some clustering is addressed by using the intra-cluster correlation coefficient at the time of analysis. However, bias can come from the post-randomisation recruitment of patients. This bias is addressed by streamlining patient questionnaires, limiting post-randomisation selection bias, and reporting outcomes at both the cluster and individual level [21]. Under-recruitment by certain GPs can exacerbate imbalances, so a study coordinator blinded to treatment assignment will contact participating GPs within two weeks of the training and regularly thereafter to ensure that the inclusion process is functioning at their site.

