**Methods:**

This is a pragmatic cluster-randomized controlled superiority trial with block randomization at the GP level in private practice in French-speaking Switzerland. GPs will be blinded to the arm allocation. The intervention is a half-day training course teaching an ‘opt-out’ approach to smoking cessation using an encounter decision aid (paper or electronic). GPs in the enhanced usual care group receives a brief refresher training about smoking cessation without changing their behaviour. GPs in both arms will recruit 23 patients each prior to routine primary care visits. The primary outcome is the effect of consulting a GP who received the intervention on the 7-day, point prevalence, smoking abstinence 6 months after the baseline appointment. Secondary outcomes include continuous abstinence; number of quit attempts; use of smoking cessation aids; patient-perceived involvement in discussions; and changes in GP behaviour. Patient outcomes will be collected using paper and telephone questionnaires. Assuming 15% drop-out, recruiting 46 GPs with 23 patients each will give us 80% power to detect an increase in smoking cessation from 4% (control) to 10.5% (intervention), with an alpha < 0.05.

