### Sample size and power calculation

Based on previous research, we expect approximately 4% of current smokers seen with usual care conditions will report having quit smoking at 6 months after a baseline visit (32). This is based on a model whereby 20% of current smokers discuss a quit attempt (higher than usual with Hawthorne effect) (11), 10% get a specific pharmacologic aid or e-cigarette, and 4% successfully quit. We anticipate a 100% increase in the number of quit discussions in the intervention arm, so about 40% of current smokers discuss a quit attempt. Subsequently, 20% will use a pharmacologic aid or e-cigarette, and 10.5% will successfully quit. For the primary outcome will use mixed effect models accounting for clustered, repeated measures; without adjusting for baseline patient characteristics, we will compare two proportions, using a two-sided test for significance, β = 0.80, α = 0.05, and an intraclass correlation coefficient of 0.03. With these parameters, we need 20 clusters (i.e. individual GPs) in each arm, each with 20 current smokers who consent to inclusion. Assuming 15% drop-out or under-recruitment by individual GPs, we will aim to recruit 46 GPs with 23 patients each, so 1,058 patients. Individual GPs will be capped at 25 patients. No specific interim or safety analyses are planned. STATA version 16.0 for Windows (StataCorp LLC, College Station, USA) will be used for all statistical analyses. Stopping rules for the study: Recruitment of GPs will end when 46 have signed a contract to complete the training program and undergone randomization. Patient recruitment will end when all participating GPs have included ≥ 20 patients and 1,060 patients have been recruited overall. GPs will be considered inactive if they have not recruited patients within the last 6 months. The trial will also end if GP recruitment has ceased and all GPs have completed recruitment. If recruitment is too low (< 200 patient participants 12 months after beginning GP training programs), new recruitment strategies will be put in place and the study may be terminated.

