#### Baseline patient and GP factors that may be associated to the primary endpoint

Numerous parameters will be collected from GPs and patients that could influence the difference in smoking cessation between the intervention and control groups. These variables, summarized in Appendix Table 3, will be compared between groups to ensure adequate randomization and allow stratified analyses of the primary result. For patients, we will collect information about socio-demographic characteristics, health literacy, reasons for seeking medical care, smoking behaviours, and baseline motivation to quit smoking. For GPs, we will collect information about socio-demographic characteristics, personal tobacco consumption, practice characteristics, and baseline practices regarding smoking cessation.

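### Patients are enrolled by GPs who are already randomised and trained; the measures said to address the resulting bias cannot correct it, and the primary comparison is described as unadjusted

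*Protocol article*

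**What the plan says.** The Participant's timeline and Recruitment sections have each GP begin recruiting patients straight after the training, from people attending routine visits. The section Controlling for contamination and other potential biases accepts that recruitment after randomisation can cause bias, and continues: "This bias is addressed by streamlining patient questionnaires, limiting post-randomisation selection bias, and reporting outcomes at both the cluster and individual level". The Discussion lists the same feature as a weakness.

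For the primary outcome, the Sample size and power calculation section says: "without adjusting for baseline patient characteristics, we will compare two proportions". The Statistical methods section specifies logistic regression with cluster-robust standard errors for binary outcomes at 6 months and names no covariate.

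The section on baseline factors collects, among other items, "smoking behaviours, and baseline motivation to quit smoking". It gives these variables two uses: comparing the arms, which it presents as a check that randomisation was adequate, and stratified analyses of the primary result.

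The Consent section places inclusion just before the visit. The Protocol amendments section reports a later change "to allow patients to complete the consent and T0 questionnaire at home and return directly to the central study site".

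**The concern.** The patients were not randomised. They are chosen, and agree, after their GP has been taught one of two approaches. The intervention training teaches GPs to offer treatment to every smoker. That may change whom they invite. It may also change when they judge a complaint too urgent for even a brief talk about smoking, which is a patient exclusion criterion. Motivation to quit plausibly predicts quitting, so a difference in motivation between arms would shift the 6-month comparison with no intervention effect at all, and could equally hide a real one.

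Three measures are said to deal with this. Streamlined questionnaires lower the burden of taking part but do not equalise who is invited. Limiting selection bias restates the aim and names no procedure. Reporting at cluster and individual level shows the same patients twice. The intraclass correlation, mentioned in the same section, corrects the variance and not the bias. Adjustment for measured prognostic variables would act on the estimate itself, and the plan as written does not include it in the primary comparison.

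**Working it through.** **1. The plan's own figure.** Inputs from the sample size section: "approximately 4% of current smokers seen with usual care conditions will report having quit smoking at 6 months" in the control arm, "and 10.5% will successfully quit" in the intervention arm, two-sided α 0.05, power 80%, ICC 0.03, 20 patients per GP.

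- Two proportions, pooled variance, no continuity correction: n = [1.96·√(2·0.0725·0.9275) + 0.8416·√(0.04·0.96 + 0.105·0.895)]² / 0.065² = 249 per arm.
- Design effect: 1 + (20 − 1)·0.03 = 1.57.
- 249 × 1.57 = 390.9 per arm; 390.9 / 20 = 19.5, so 20 GPs per arm.
- With 400 per arm the effective size is 400 / 1.57 = 254.8 and the power 81.0%.

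The stated 20 GPs of 20 patients reproduces as an unadjusted test. The figure is not in dispute. The inflation covers variance only and gives no protection against a differing mix.

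**2. Room for selection.** A GP at the minimum of 80 patients a month, with about a quarter smoking (the Background's population figure), sees roughly 80 × 0.25 = 20 smokers in one month. Over six months with no repeat visits that is up to 120, for 23 places. Both ends are rough, since eligibility requires daily use and patients return. The article states no consecutive-enrolment rule.

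**3. Size of a spurious difference, on assumed mixes.** The documents give neither the share of motivated smokers nor its link to quitting. Assume no true effect, a control quit rate of 4%, 30% of control enrolees motivated, and motivated smokers quitting R times as often as the others. With a share m motivated in the intervention arm:

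- quit rate in unmotivated smokers b = 0.04 / (0.3R + 0.7)
- intervention-arm rate p = b·(mR + 1 − m)
- rejection by the nominal 5% two-sided test, at 254.8 effective patients per arm

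| R | m | p | Difference (points) | Rejection |
|---|---|---|---|---|
| 2 | 20% | 3.69% | −0.31 | 5.4% |
| 2 | 40% | 4.31% | +0.31 | 5.3% |
| 2 | 50% | 4.62% | +0.62 | 6.3% |
| 3 | 20% | 3.50% | −0.50 | 6.0% |
| 3 | 40% | 4.50% | +0.50 | 5.9% |
| 3 | 50% | 5.00% | +1.00 | 8.5% |
| 4 | 20% | 3.37% | −0.63 | 6.7% |
| 4 | 40% | 4.63% | +0.63 | 6.4% |
| 4 | 50% | 5.26% | +1.26 | 10.4% |

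**4. Steeper assumptions.** Let motivated smokers quit at 10% and others at 2.5%, with 20% of control enrolees motivated: 0.2·0.10 + 0.8·0.025 = 4.0%. A 40% share in the intervention arm gives 0.4·0.10 + 0.6·0.025 = 5.5% (+1.5 points, rejection about 12.5%). A 60% share gives 0.6·0.10 + 0.4·0.025 = 7.0% (+3.0 points, about 32%). The motivated share must double or triple to reach these values.

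**5. How many covariates the data can carry.** Expected quitters at 400 per arm: 400·0.04 + 400·0.105 = 16 + 42 = 58. Blocks of two or four among 46 GPs give 46/2 = 23 down to 46/4 = 11.5, so about 12 to 23 blocks.

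**The case against.** **The unadjusted wording is in the sample size paragraph.** It runs into α, power and ICC and could be read as a power assumption, with covariates left to an analysis plan that is not shown. This lowers confidence. Still, the sentence is stated for the primary outcome and nothing elsewhere in the article alters it.

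**The plan does more than the quoted sentence says.** GPs and patients are not told how the trainings differ, inclusion is placed before the visit, enrolment is kept brief to draw in less motivated patients, and a coordinator follows up inclusion. These steps are preventive and may reduce the bias. They are incomplete: the Blinding section concedes that intervention GPs will notice that their training is unusual, and it is the training content itself that may alter recruitment.

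**Stronger readings that the documents do not support.** A reader might infer that the baseline data serve only as a balance check, so that a positive result could not be told apart from case-mix. But stratified analyses of the primary result are planned, and they would be informative. A reader might also infer that the bias favours the intervention. Teaching GPs to approach every smoker could just as well bring in less motivated patients and pull the result towards the null. Finally, the amendment on home completion does not say that the baseline questionnaire follows the consultation; that is a possibility to check.

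**Conclusion.** The point holds, and the plan should be changed. The bias is acknowledged but described as dealt with, on the strength of measures that cannot correct a differing patient mix. The primary comparison is described as unadjusted although likely prognostic variables are collected.

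Neither size nor direction can be derived from the documents. On the moderate mixes, the spurious difference of −0.6 to +1.3 points is at most about a fifth of the 6.5-point target (1.26 / 6.5 = 19%), with type I error up to about 10%. Rejection rates of 12.5% to 32% arise only under the steep assumptions and should not be taken as expected. All these figures assume no true effect and selection on a single measured trait. Adjustment would remove that measured part and nothing beyond it.

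**What to change.** - Pre-specify the primary 6-month logistic model, with cluster-robust standard errors, as adjusted for a short set drawn from the baseline items: age, sex, daily tobacco consumption or dependence, and baseline motivation. Report a standardised risk difference. Keep the unadjusted result as a sensitivity analysis.
- Record whether the baseline questionnaire was completed before or after the visit. If motivation can be rated after the visit, leave it out of the primary model, because the consultation may have changed it. Use it instead in a sensitivity analysis restricted to patients with a pre-visit questionnaire.
- Do not add training-date blocks as fixed covariates: 12 to 23 levels are too many for about 58 events.
- In the section on contamination and bias, describe the bias as partly mitigated. In the section on baseline factors, present the comparison of arms as a description of recruitment balance and not as assurance about randomisation.

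The cost is analysis-plan wording and one data field, with some missing covariate values to handle and an odds ratio that becomes conditional on the covariates. Selection on unmeasured traits remains, and should be stated as a limitation. The covariates should be fixed before unblinding, so that the adjustment cannot look data-driven.
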